## Intervention procedures

### Randomization and intervention protocol

At baseline, participants will be randomly assigned to receive either sham stimulation (delayed-start group) or active tDCS (early-start group). The placebo group will receive double-blinded sham procedure for 2 days. On Day 3, all participants will receive the active tDCS intervention as an adjunctive treatment for up to day 14. The allocated intervention will not be modified.

At baseline, participants will be randomly assigned to one of two arms for each focal event:

In the **Early Start Group** participants will receive 20 min of active tDCS daily from the start of the intervention period (day 1) for up to 14 days. By default, each active stimulation treatment session starts with an automated ramp up of current to 2 mA over 15 s to keep participants blind to the intervention. For the early start group tDCS then continues for 20 min until it ramps down.

In the **Delayed Start Group** participants will receive sham-stimulation/placebo treatment on day 1 and day 2 of the intervention followed by up to 12 additional days of active tDCS (1x daily for 20 min). Like active tDCS, sham tDCS starts with an automated ramp up of current (from 0 to 2 mA over 15 s) to mimic the sensations observed with active tDCS and to keep participants blind to the intervention. For the sham tDCS the current stops after the 15s ramp up. This sham stimulation protocol is well supported by current literature [16, 17].

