## Statistical methods

### Statistical analyses

The data will be tabulated using descriptive statistics. Mean and standard deviation will be reported for continuous data. Median and range will also be reported for skewed data. Categorical data will be described using percentages and frequencies.

The primary analysis of the binary outcome of a 50% reduction in epilepsy frequency (number and duration of seizures, jerks/min) from baseline (counted on day 0) will be completed by applying a generalised estimating equation to thus obtain robust standard errors and test whether the tDCS group improves more rapidly than the sham group.

Further analysis will consider a more complex model incorporating random slopes where appropriate. Sensitivity analysis for missing data will also be investigated. Other outcome data will be analysed as appropriate using a mixed effects model for continuous data and a generalised estimating equation for binary, categorical or count data with appropriate distribution and link function.

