#### Target difference and sample size

Assuming a minimum of one assessment per patient event per day, each event will contribute 14 data points over 14 days of treatment (tDCS or sham). Further assuming no association between days of treatment and reduction in epilepsy events, the outcome data are treated as clustered data for the purposes of the power calculation. Assuming 5% type I error, 90% power, and 10% intra-patient correlation, 28 patient events will be required over 14 days of treatment to detect an improvement of 20% in events that achieved 50% reduction in seizure frequency. The sample size calculation also assumes that only 10% of the events in the placebo group will achieve 50% reduction in epilepsy frequency from baseline (on day 0). To account for drop-out, 30 patient events will be required for this study. The patient events will be allocated equally to active and sham tDCS groups. These calculations were determined based on clinical significance, patient perspectives, historical data, statistical considerations, and regulatory guidelines [25].

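### The primary GEE compares tDCS with a sham group that exists only on days 1–2; over the 14 days used for the sample size the planned contrast almost disappears, and a slope test can favour the delayed arm

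*Protocol article*

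**What the plan says.** All references are to the Protocol article.

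- *Statistical analyses*: the binary outcome of a 50% reduction from day 0 is analysed by a generalised estimating equation, to "test whether the tDCS group improves more rapidly than the sham group". No days and no model terms are given.
- *Randomization and intervention protocol*: "The placebo group will receive double-blinded sham procedure for 2 days", and then "On Day 3, all participants will receive the active tDCS intervention as an adjunctive treatment for up to day 14". *Intervention administration and assessment procedures* repeats the crossover on day 3. *Intervention allocation* sets the second device permanently to active for sessions 3 to 14.
- *Target difference and sample size*: "each event will contribute 14 data points over 14 days of treatment (tDCS or sham"). The section continues: "Further assuming no association between days of treatment and reduction in epilepsy events", the data are treated as clustered. The remaining inputs are "Assuming 5% type I error, 90% power, and 10% intra-patient correlation", a target to "detect an improvement of 20% in events that achieved 50% reduction in seizure frequency", and a control rate that "assumes that only 10% of the events in the placebo group will achieve 50% reduction in epilepsy frequency". The result is 28 events, raised to 30 for drop-out.

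**The concern.** The stated contrast does not fit the stated design. After day 2 there is no sham group, only an arm that started two days later. The analysis section nevertheless speaks of a sham group without limiting the days, and the sample size treats each event as staying on one treatment for all 14.

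There is a second mismatch. The sample size assumes that response does not depend on day, so it is powered for a difference in level. The primary test is worded as a difference in speed. If response is constant within a treatment, the only change over time in this design is the delayed arm's rise at day 3, which a slope test would credit to the delayed arm.

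At stake is the trial's main conclusion. On the 14-day basis that the sample size uses, an effective treatment could give a null primary result, or a significant one that appears to favour starting later.

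**Working it through.** **Inputs from the documents:** 10% control response; a 20-point improvement, hence 30%; alpha 0.05; power 0.90; intra-patient correlation 0.10; 14 daily points per event; 1:1 allocation; sham on days 1–2 only.

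**Assumptions added here:** a two-sided test (not stated, but it reproduces the plan's figure); as base case, an immediate step from 10% to 30% once active treatment starts; no early stopping, so every event gives 14 points.

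**1. The plan's own figure.** Two proportions, 0.10 v 0.30, two-sided 0.05, 90% power: 82 independent observations per arm. Design effect = 1 + 13 × 0.10 = 2.3. Events per arm = 82 × 2.3 / 14 = 13.47, so 14 per arm and 28 in total. This matches, with 91% power after rounding up. It holds only if the control arm stays at the sham rate for all 14 days.

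**2. The 14-day arm effect under the actual design.** Delayed-arm average = (2 × 0.10 + 12 × 0.30) / 14 = 0.2714. Difference = 0.30 − 0.2714 = 0.0286, or 2.9 points. Effective size per arm = 14 × 14 / 2.3 = 85.2. Power for a result in favour of early start is 6.1% with 28 events and 6.3% with 30. A simulated GEE with 15 events per arm gave 7.2%. Ninety per cent power would need 5,252 × 2.3 / 14 = 862.8, so 863 per arm and 1,726 events. With 30 events and a correlation anywhere from 0.05 to 0.90, power stays between 7.3% and 3.8%.

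**3. The 14-day arm-by-day slope.** In the base case the early arm is flat at 30% and the delayed arm steps up at day 3. The fitted linear slope of the early arm minus that of the delayed arm is −1.05 points per day (log odds ratio −0.054 per day). Adding day 0 as non-response in both arms leaves it negative, at −0.79 points per day. Logistic GEE with robust standard errors, 15 events per arm, 250 simulated trials per scenario (response shapes are assumptions):

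| Response to active tDCS | Slope difference, log OR/day | Significant for early arm | Significant for delayed arm |
|---|---|---|---|
| Immediate, 10% to 30% | −0.054 | 0% | 20% |
| Builds over 3 days to 30% | −0.049 | 0% | 18% |
| Builds over 7 days to 30% | −0.038 | 0.4% | 12% |
| Builds linearly over 14 days to 30% | −0.008 | 1.2% | 3.6% |
| Accelerates over 14 days, 10% to 60% | +0.029 | 8.4% | 1.2% |

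A larger simulation of the first row (6,000 trials, 28 events) gave 21.7% for the delayed arm and 0.2% for the early arm; a further one gave about 23% and 0%.

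**4. Days 1–2 only.** The 20-point contrast is intact. Design effect = 1 + 1 × 0.10 = 1.1. Effective size per arm = 14 × 2 / 1.1 = 25.5, giving 42.8% power; with 15 per arm it is 27.3, giving 45.3%. Simulated GEEs at 28 events gave 37–39%. Ninety per cent power would need 82 × 1.1 / 2 = 45.1, so 46 per arm and 92 events.

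**The case against.** The strongest reply is that *Statistical analyses* fixes neither a window nor model terms. The 14-day count comes from the sample-size section, where clustering is adopted for the power calculation only. *Blinding* says that a statistical analysis plan will be finalised before unblinding; it is not shown and could restrict the test to days 1–2. That stands: the article does not prescribe a 14-day main effect or a linear slope.

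Other readings also avoid the problem: day as a factor with early contrasts, time to response, or a model of the treatment currently received. A simulation of the last (28 events, latent correlation 0.2, 400 trials, no other day effect) rejected in the right direction in about 57% of trials and in the wrong direction in none. With a day-3 period term the figure was about 37%, the same as days 1–2 alone. About 4% of the 14-day fits failed.

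A reader might therefore infer too much: that the primary test cannot detect the effect, or points the wrong way whenever tDCS works. The documents do not support either. The reversal needs both a linear slope over 14 days and a fairly quick response. It vanishes for a slow build-up and changes sign for an accelerating one, and the long-term synaptic mechanism in the Background leaves gradual response possible. A quick response is nevertheless the trial's own expectation: the Discussion reports that episodes may resolve within three days and bases the delayed start on that.

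Finally, treatment ends at resolution, so many events may give fewer than 14 points. This was not modelled, and the percentages are illustrations under the plan's inputs.

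None of this removes the contradiction. If the unseen plan restricts the test to days 1–2, the direction is safe but the sample-size section is then wrong for that test.

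**Conclusion.** The concern holds in conditional form. The article names a comparison with a sham group and sizes it over 14 days, in a design with two days of sham; those sections cannot all stand. If the GEE is fitted over the 14 days, then under the plan's inputs, an immediate effect and no early stopping, the arm difference falls from 20 to about 2.9 points and power from about 91% to about 6–7%. A linear arm-by-day slope on the same basis is significant for the wrong arm in about 20–23% of simulated trials and for the right one in about 0%. The loss of contrast follows from simple averaging and is firm. The reversal depends on the model chosen and on the speed of response. The point needs correcting before unblinding because it concerns the test that decides the trial.

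**What to change.** In *Statistical analyses*:

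- Name the arms early-start and delayed-start.
- Replace the wording on more rapid improvement with a primary contrast of responder status between arms in the sham-controlled window, from after the day-1 session to before the day-3 session.
- State that neither a 14-day arm effect nor a linear arm-by-day slope is the primary test.
- Report days 3–14 as secondary, described as active treatment in both arms.

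In *Target difference and sample size*, replace the 14 days of tDCS or sham, and the assumption of no day effect, with a calculation for that window.

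The cost is a wording change in the protocol and analysis plan, with the same data collected. The downside is that fewer observations enter the primary test, so the stated 90% power must be restated at about 43–45% with 28–30 events. Whether that is acceptable is a separate decision for the sponsor.

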### Interim analyses

No interim analyses are planned.

#### Target difference and sample size

Assuming a minimum of one assessment per patient event per day, each event will contribute 14 data points over 14 days of treatment (tDCS or sham). Further assuming no association between days of treatment and reduction in epilepsy events, the outcome data are treated as clustered data for the purposes of the power calculation. Assuming 5% type I error, 90% power, and 10% intra-patient correlation, 28 patient events will be required over 14 days of treatment to detect an improvement of 20% in events that achieved 50% reduction in seizure frequency. The sample size calculation also assumes that only 10% of the events in the placebo group will achieve 50% reduction in epilepsy frequency from baseline (on day 0). To account for drop-out, 30 patient events will be required for this study. The patient events will be allocated equally to active and sham tDCS groups. These calculations were determined based on clinical significance, patient perspectives, historical data, statistical considerations, and regulatory guidelines [25].

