## Discussion

### Study design, practical and operational challenges

Refractory focal epilepsy associated with a mitochondrial disorder, while rare, often has a poor prognosis. Here, we address the unique challenges encountered in designing a randomized, sham-controlled study within the context of rare diseases.

First, designing this randomised sham-controlled study has posed ethical challenges of administering a treatment to one group and not another while keeping high methodological stringency. Our team’s prior treatment of five patients with mitochondrial epilepsy, who had received cathodal tDCS on compassionate grounds, suggests that focal episodes may resolve within the first three days of stimulation [27]. Based on that, we adopted a delayed-start design. One group receives the treatment immediately (early-start), while the delayed-start group receives a non-active (sham) treatment for the first two days and then receives active treatment from day 3.

Secondly, recruiting patients with a condition classified as a rare disease who experience an acute event is logistically challenging and, in this case, requires active recruitment methods. Potential participants will be identified by their health care provider while patients are admitted to the hospital for an acute focal epileptic event that remains unresolved by antiepileptic drugs. Consequently, the timeframe of recruitment is unpredictable, and to complete recruitment within the 3-year study period, individual means of recruitment may be considered.

Third, for some participants admission to our premises could be disruptive e.g., if their symptoms can be managed externally. To not exclude any potential participants from entering the study, we consider remote treatment for those patients. In that case patients would be referred to our site for their tDCS treatment. After initial supervised device training, tDCS will be self-applied by patients at home or in their care setting, under the remote supervision of a medical professional. Depending on the participants’ circumstances, we will determine individually which option is least disruptive.

Fourth, patients exhibit various types of seizures, each requiring unique methods of recording and diagnosis. To ensure optimal daily monitoring of seizure activity, we maintain close monitoring of the patient, provide flexible seizure diary templates, and record relative values.

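### The 90% power is calculated for a constant difference in responder level, but the primary test is stated as faster improvement, for which the sizing assumes no effect over days 1–14

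*Protocol article*

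**What the plan says.** Under *Target difference and sample size*, each event is taken to give 14 daily data points, treated as clustered. The inputs are: "Assuming 5% type I error, 90% power, and 10% intra-patient correlation". The control rate is that "only 10% of the events in the placebo group will achieve 50% reduction in epilepsy frequency from baseline", and the target is "to detect an improvement of 20% in events that achieved 50% reduction in seizure frequency". I read this as 30% against 10%. The time pattern is set aside explicitly: "Further assuming no association between days of treatment and reduction in epilepsy events". The result is 28 events, raised to 30 for drop-out and split equally.

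Under *Statistical analyses*, the primary outcome is binary (50% reduction from day 0) and is analysed by a generalised estimating equation (GEE) with robust standard errors, to "test whether the tDCS group improves more rapidly than the sham group". No regression term is given. Random slopes appear only afterwards, under further analysis.

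Under *Randomization and intervention protocol*, the delayed-start arm receives sham on days 1 and 2 and active stimulation from day 3. The *Discussion* supports this design with five patients treated on compassionate grounds, which suggested that "focal episodes may resolve within the first three days of stimulation".

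**The concern.** The two sections describe different hypotheses. The sizing concerns a gap in level that is the same every day. The primary test, as worded, concerns how quickly each arm gets better. If response has no association with day in either arm, the two arms have the same (zero) change across days 1–14, however far apart their levels are. The effect that the trial is sized to detect is then invisible to a test of change over those days.

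A reader of the article would take 90% to be the power of the primary analysis. If speed is tested as a difference in trend, a sustained 20-point benefit of the planned size would usually be missed. The flat assumption also fits poorly with the plan's own reasoning: the design rests on early resolution, and the control arm changes treatment on day 3. Both lead one to expect response to vary with day.

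**Working it through.** **1. Reproduce the 28.** Inputs from the sample-size section: 10% v 30%, 5% type I error (two-sided assumed, as this reproduces the figure), 90% power, correlation 0.10, 14 days. Pooled formula for two proportions, mean 0.20:

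n = [1.96·√(2·0.2·0.8) + 1.2816·√(0.09 + 0.21)]² / 0.20² = (1.1087 + 0.7019)² / 0.04 ≈ 82 observations per arm.

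Design effect = 1 + 13·0.10 = 2.3. Events per arm = 82·2.3/14 = 13.47, so 14 per arm and **28 in total**. The match is exact, and the formula contains no time term.

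Power at 14 per arm: effective n = 14·14/2.3 = 85.2, and (0.20·√85.2 − 1.1087)/0.5477 = 1.346, giving 91.1%. At 15 per arm it is 92.9%.

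**2. Test speed under the same alternative.** With constant probabilities in each arm, the arm-by-day coefficient over days 1–14 is zero on any link scale. Simulated events (beta-binomial, correlation 0.10, 14 daily outcomes, flat 10% v 30%) were fitted by logistic GEE with robust standard errors. Rejection rates:

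| Events per arm, working correlation | Arm-by-day, plain | Arm-by-day, small-sample corrected | Arm only (level), plain |
|---|---|---|---|
| 14, exchangeable (1,000 runs) | 6.5% | 4.2–4.8% | 91.3% |
| 14, independence (5,000 runs) | 8.7% | 6.4% | 91.0% |
| 15, exchangeable (1,000 runs) | 9.4% | 6.7–7.8% | 92.1% |
| 15, independence (5,000 runs) | 8.2% | 6.5% | 92.9% |

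The excess over 5% in the arm-by-day columns is mostly small-sample inflation of the sandwich estimator. It is not power.

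**3. Try assumed time courses.** The documents give none, so these only illustrate the range. All have control flat at 10%, tDCS averaging about 30% (slightly less for the second curve), and sham for all 14 days:
- linear rise from 10% to 50%: arm-by-day rejects about 67%;
- rise over three days, then flat at 30%: about 14%;
- linear rise from 2% to 58%: about 87–91% across separate runs.

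The power of a speed test therefore depends almost wholly on a trajectory that the sizing section does not state.

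**4. Apply the actual schedule.** Assume the same rates and immediate onset. The delayed-start arm is at 10% on days 1–2 and 30% on days 3–14, an average of (2·10 + 12·30)/14 = 27.1% against 30%.
- Level contrast over all 14 days: the difference is 2.9 points. Simulated power was about 11–12%, and about 8% in a check that generated the correlation through a latent normal variable. The formula in step 1 gives about 6%.
- Arm-by-day contrast: rejects in about 21–26% of runs, almost always because the *delayed* arm's slope is steeper.
- Level contrast over days 1–2 only: design effect 1 + 1·0.10 = 1.1. Effective n = 14·2/1.1 = 25.5 or 15·2/1.1 = 27.3 per arm, giving power of **42.8% and 45.3%**.

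**The case against.** The strongest reply is that the article never writes an arm-by-day term. It names a GEE on a binary outcome and mentions slopes only under further analysis, so the primary contrast may be a simple arm effect, with the detail left to the analysis plan. Also, the outcome is a reduction from day 0, so every event starts as a non-responder. An arm at 30% from day 1 has, in ordinary language, improved faster than one at 10%. Finally, the no-association assumption is offered as a simplification for the power calculation, and the early-resolution remark comes from five compassionate-use patients and is worded tentatively, so it does not firmly contradict that assumption.

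Much of this stands. The 4–9% figure is conditional on testing change within days 1–14. It is not established as the trial's power. The reply does not remove the mismatch, though. If a level contrast is meant, the sentence defining the primary test is wrongly worded. If speed is meant, the power statement is for something else. A separate analysis plan may supply the model term, but it cannot make these two published statements agree.

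A reader might also infer that no plausible time course gives a speed test 90% power, or that 28–30 events are simply too few. The documents do not support either. They give no trajectory, and a steep steady rise from near zero reaches about 90%. Nor is 28 an arithmetic error, since it is correct for a different test.

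**Conclusion.** The point holds in conditional form. The 90% is the power for a constant 20-point difference in daily responder proportion. The stated primary test is of faster improvement. If that is tested as a difference in change over days 1–14, the sizing alternative is a null case and rejection is about the type I error (roughly 4–9%). This rests on that reading of the test, on two-sided 5%, on correlation 0.10 and, for the comparison with 90%, on the sizing section's own premise of 14 days of each condition.

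It is tempting to conclude that renaming the primary test as a level contrast would recover the 90%. It would not. With sham on days 1–2 only, a 14-day level contrast has about 11–12% power or less under the same rates and immediate onset, and a contrast confined to days 1–2 has about 43–45%. The two sections have to be reconciled together with the treatment schedule.

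**What to change.** Name one primary contrast under *Statistical analyses* and restate the power under *Target difference and sample size* for that contrast, on the schedule given under *Randomization and intervention protocol*. There are two workable forms:

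(a) Make the primary contrast the arm difference in responder proportion over the sham-controlled days 1–2, move the speed question to a secondary analysis, and replace 90% with the power this gives: about 43–45% with 14–15 events per arm, 10% v 30% and correlation 0.10.

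(b) Keep speed as primary, write out the term that is tested, delete the no-association assumption, state the assumed time course in each arm including the day-3 crossover, and recalculate the power for that test.

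Do not use a level contrast averaged over all 14 days, and do not attach 90% to any of these contrasts without recalculation.

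The cost is wording in two sections, one power re-run and a less favourable stated power. No extra patients are needed to make the statement correct. The change should be made before unblinding, which the *Blinding* section already places after the analysis plan is finalised.

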## Assessment and collection of outcomes

### Pre-intervention screening

Following informed consent, participants will undergo the following screening assessments to confirm eligibility for the study:

Collection of basic demographic information (name, address, date of birth, NHS number).Collection of full medical history.Physical examination and vital signs (height, weight, heart rate, respiration rate, blood pressure and head circumference).Baseline seizure frequency assessment through seizure diary and video assessment on day 0.

These assessments will be documented in the participant’s hospital records.

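### The 90% power rests on an unsupported 10% within-event correlation with almost no slack; scoring every day against one shared day-0 value probably pushes the correlation higher

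*Protocol article*

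**What the plan says.** All from the protocol article.

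- Target difference and sample size: "each event will contribute 14 data points over 14 days of treatment (tDCS or sham"), and "the outcome data are treated as clustered data for the purposes of the power calculation". The result is "Assuming 5% type I error, 90% power, and 10% intra-patient correlation, 28 patient events will be required over 14 days of treatment".
- Same section: the trial is sized "to detect an improvement of 20% in events that achieved 50% reduction in seizure frequency", with a control rate under which "only 10% of the events in the placebo group will achieve 50% reduction in epilepsy frequency from baseline (on day 0"). On allocation: "The patient events will be allocated equally to active and sham tDCS groups". The total is then raised from 28 to 30 for drop-out.
- Statistical analyses: the binary outcome is a 50% reduction "from baseline (counted on day 0) will be completed by applying a generalised estimating equation", with robust standard errors.
- Pre-intervention screening: "Baseline seizure frequency assessment through seizure diary and video assessment on day 0". Table 1 allows at most 15 diary days against at most 14 stimulation days, so baseline is one day.

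The basis given for the assumptions is a general list of considerations. There is no derivation of the 10%, no day-to-day variance, and no sign that the shared baseline was allowed for.

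**The concern.** The within-event correlation is what lets 14 events per arm count as far more than 14 observations. A responder day is one with seizure frequency at or below half the day-0 value, and all 14 days of an event use that one value. If day 0 happens to be high, most later days look like responses; if it happens to be low, few do. The days are therefore positively correlated even if they are otherwise independent and events do not differ in true response.

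If that correlation exceeds 10%, the trial has less power than stated, and a null result could be read as coming from a better-powered trial than it was. This is separate from how many sham days are available for comparison, because it arises even with 14 full days in each arm.

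**Working it through.** **Inputs (Target difference and sample size).** Control 10%, active 10% + 20% = 30%, type I error 5% (taken as two-sided), power 90%, m = 14 days per event, correlation (ICC) 0.10, 1:1 allocation. The cluster is the event, which is the protocol's experimental unit.

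**Step 1: reproduce the 28.** The pooled two-proportion formula gives

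n = [1.96·√(2·0.20·0.80) + 1.2816·√(0.10·0.90 + 0.30·0.70)]² / 0.20² = [1.96·√0.32 + 1.2816·√0.30]² / 0.04 ≈ 82 per arm.

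The design effect is 1 + 13·0.10 = 2.3. Then 82·2.3/14 = 13.5, so 14 events per arm and 28 in total. This matches exactly. Other conventions do not: unpooled variance gives 26, a continuity correction 32 and a one-sided test 24.

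**Step 2: slack.** Fourteen events by 14 days is 196 observations per arm. With D = 1 + 13·ICC,

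power = Φ{[0.20 − 1.96·√(0.32·D/196)] / √(0.30·D/196)}.

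| ICC | D | Power, 28 events | Power, 30 events | Events for 90% |
|---|---|---|---|---|
| 0.10 | 2.30 | 91% | 93% | 28 |
| 0.16 | 3.08 | 81% | 84% | 38 |
| 0.20 | 3.60 | 75% | 78% | 44 |
| 0.25 | 4.25 | 68% | 71% | 50 |
| 0.32 | 5.16 | 59% | 62% | 62 |

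Power is 90% when 196/D = 82, that is D ≈ 2.39 and ICC ≈ 1.39/13 = 0.107. Simulation of beta-binomial data with a t-test on event means agrees: 90% at 0.10, 81% at 0.16 and 60% at 0.32.

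**Step 3: correlation from the shared baseline alone.** Let X₀ be the day-0 value and Xₜ the value on day t. Day t is a response if Xₜ ≤ 0.5·X₀. Days are taken as independent, with no true differences between events. The noise is set so that 10% of sham days respond, and the active mean is lowered until 30% respond. These noise models are assumptions; the protocol gives none.

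- *Log-normal, equal variance on all days.* The log ratios share log X₀, so their correlation is 1/(1+1) = 0.50. Dichotomised, the ICC is 0.249 at 10% and 0.318 at 30%. Weighted by binomial variance: (0.09·0.249 + 0.21·0.318)/0.30 = 0.30.
- *Normal, constant absolute SD.* Xₜ − 0.5·X₀ has variance 1.25σ² and covariance 0.25σ², so the correlation is 0.20. Dichotomised, this is 0.080 and 0.119, pooled 0.107.

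| Day-to-day model | ICC sham / active | Pooled ICC | Power, 28 events |
|---|---|---|---|
| Normal, constant absolute SD | 0.08 / 0.12 | 0.107 | 90% |
| Log-normal, day-0 variance one quarter of later days | 0.08 / 0.12 | 0.107 | 90% |
| Poisson | 0.12 / 0.19 | 0.17 | 80% |
| Normal, constant CV | 0.08 / 0.23 | 0.18 | 77% |
| Negative binomial (mean 20 to 500 per day) | 0.15-0.18 / 0.23-0.28 | 0.21-0.25 | 67-74% |
| Log-normal, equal variance | 0.25 / 0.32 | 0.30 | 62% (simulated 63%) |

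**Step 4: true differences between events.** These come on top. Lasting differences in change from baseline equal to 10%, 20% and 30% of the daily variance move the constant-SD normal case to ICC 0.14, 0.17 and 0.20, with power 84%, 79% and 75%. In the log-normal case, 10-30% gives ICC 0.31-0.35 and power 60-56%.

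**The case against.** The case for the plan has real force.

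- *The 10% is a declared assumption and the 28 follows from it.* This stands. The issue is support for an input, not arithmetic.
- *The documents do not fix the correlation.* This stands. A reader might infer that the endpoint forces a value of 0.16-0.32 and that 90% is therefore false. The text does not support that: it gives no seizure level, distribution or day-to-day variance, and the endpoint also takes in duration and jerks per minute. Nor does a value near 0.10 always need day 0 to be steadier than later days. That condition belongs to the log-normal model; with a constant absolute SD, equal variances give 0.107.
- *Much higher values are tempting but break the sizing's premises.* If response meant permanent resolution, the correlation would be about 0.6, and with one outcome per event it would be 1. The sizing assumes no association between day and response and treats the days as clustered observations, so neither is a fair reading of it.
- *The losses are for 14 days per arm, whereas sham lasts two days.* This stands as a limit on scope. With two days per arm the same formula gives 43% at ICC 0.10 and 37% at 0.32, so the correlation then matters far less than the number of days compared.
- *Robust standard errors deal with clustering.* They address the validity of the test, and no bias is alleged here. They do not restore power.

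One reply remains. In the two favourable models the shared baseline by itself uses up the whole 10% allowance and leaves nothing for true differences between events.

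**Conclusion.** The concern holds as a question of support for an input. The 28 events are correctly computed from the stated assumptions. The 10% correlation is unsupported and probably too low for an endpoint in which all days share one day-0 reference, and the calculation has no room for error beyond about 0.107. On the sizing's own 14-days-per-arm premise, 28 events give about 90% power in the most favourable models examined and about 62-80% under count-type, constant-CV or log-normal variation, before true differences between events. So 90% is the favourable end of a range.

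This rests on assumed noise models calibrated to 10% and 30%, independent days, and a two-sided 5% test. It does not show that power must be below 90%. Severity is moderate: the change is to a stated figure and one model term, and the validity of the test is not in question.

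**What to change.** 1. In Target difference and sample size, either justify the 10% given the single shared day-0 baseline (for example from day-to-day variation in earlier patients' diaries), or replace the unqualified 90% with the power of 28 and 30 events over correlations 0.10-0.32: about 91% to 59%, and 93% to 62%. This costs one recalculation and a less favourable statement. No extra events or assessments are needed.

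2. In Statistical analyses, prespecify log day-0 seizure frequency, already collected, as a covariate in the primary generalised estimating equation. This is a recommendation; leaving covariates to an analysis plan is not itself a fault. It costs one degree of freedom. In a 14-day log-normal simulation of the binary model, power rose from 56-61% to 64-99%, with type I error of about 4-6%. The gain is larger the less events differ in their usual seizure level, and small or absent if only the two sham days are compared. With so few events, type I error also depends on how the robust standard errors are corrected for small samples, so that correction should be named.
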